## <Estimand for the Primary Objective>

Primary clinical question: In patients with SMH due to AMD or RAM, regardless of the use of VEGF-inhibitor therapy or the use of tPA formulations for other diseases, what is the change in central foveal hemorrhage volume at the 1-week time point after subretinal administration of montepilase (recombinant)?

|                                    |                                                                                                                                                                                                                 |
|------------------------------------|-----------------------------------------------------------------------------------------------------------------------------------------------------------------------------------------------------------------|
| i. Treatment condition of interest | Subretinal administration of montepilase (recombinant)                                                                                                                                                          |
| ii. Population                     | Patients with SMH defined by the inclusion criteria (severe sub-macular hemorrhage in which spontaneous resolution is not expected, the bleed involves the fovea, and marked visual-acuity loss is anticipated) |
| iii. Endpoint                      | Change from baseline to week 1 in CFT measured by optical coherence tomography (OCT)                                                                                                                            |
| iv. Other intercurrent events      | See Table 3-1                                                                                                                                                                                                   |
| v. Population-level summary        | Mean change from baseline to week 1 in CFT                                                                                                                                                                      |

Rationale for the estimand: In SMH, the thickness of the central foveal hemorrhage is known to affect visual prognosis. CFT measured by OCT represents the combined thickness of the retina and the hemorrhage at the fovea, thereby reflecting the volume of the central foveal hemorrhage and also allowing assessment of hemorrhagic pigment-epithelial detachment, which is related to visual outcome. Consequently, CFT measured by OCT was selected as the variable constituting the primary estimand. Even when considering the potential impact of VEGF-inhibitor use after montepilase administration or the use of tPA formulations for other diseases, an early reduction in OCT-measured CFT is considered important for regulatory authorities and for individuals involved in determining the therapeutic strategy for the target patient population. Moreover, the persistence of SMH adversely affects visual prognosis; therefore, early displacement of the SMH is important. Accordingly, the 1-week time point, at

which OCT measurement of CFT can be performed without interference from gas tamponade introduced during vitrectomy, was designated as the assessment time point for the primary estimand.

<Estimand for the Secondary Objective (1)>

Clinical question of interest: In patients with SMH due to AMD or RAM, regardless of the use of VEGF-inhibitor therapy or the use of tPA formulations for other diseases, what is the change in ophthalmic examination findings at the 4-week time point after subretinal administration of monteplase (recombinant)?

|                                    |                                                                                                                                                                                                                                                                                                                     |
|------------------------------------|---------------------------------------------------------------------------------------------------------------------------------------------------------------------------------------------------------------------------------------------------------------------------------------------------------------------|
| i. Treatment condition of interest | Subretinal administration of monteplase (recombinant)                                                                                                                                                                                                                                                               |
| ii. Population                     | Patients with SMH defined by the inclusion criteria (severe sub-macular hemorrhage in which spontaneous resolution is not expected, the bleed involves the fovea, and marked visual-acuity loss is anticipated)                                                                                                     |
| iii. Endpoint                      | 1) Change in CFT from baseline at Week 4.
2) Presence or absence of a foveal hemorrhage measuring $\geq 1$ disc diameter at Week 4.
3) BCVA (logMAR equivalent) at Week 4.
4) Change in BCVA (logMAR equivalent) from baseline at Week 4.                                                                  |
| iv. Other intercurrent events      | See Table 3-1                                                                                                                                                                                                                                                                                                       |
| v. Population-level summary        | 1) Mean change from baseline to Week 4 in CFT measured by OCT.
2) Proportion of patients with foveal hemorrhage measuring $\geq 1$ disc diameter observed by fundus photography at Week 4.
3) Mean BCVA (logMAR equivalent) at Week 4.
4) Mean change from baseline to Week 4 in BCVA (logMAR equivalent). |

Rationale for the estimand: SMH causes acute and severe visual impairment, and prolonged hemorrhage may induce irreversible degeneration of the neurosensory retina, thereby affecting visual prognosis. Even when considering the effects of VEGF inhibitor use after monteplase administration or the use of tPA products for other diseases, reduction of the hematoma,

displacement of the hematoma, and the degree of visual recovery are considered important for regulatory authorities and individuals involved in treatment decision-making for the target patient population. Although long-term observation is required to evaluate visual recovery, hematomas may undergo spontaneous absorption over time, and rebleeding frequently occurs. Therefore, long-term changes in CFT may be substantially influenced by factors other than subretinal tPA administration. Accordingly, one month was selected as one of the assessment time points for the secondary estimand.

<Estimand for the Secondary Objective (2)>

Clinical question of interest: In patients with SMH secondary to AMD or RAM, regardless of the use of VEGF inhibitors or tPA products for other diseases, to what extent do ophthalmologic findings change at Week 12 following subretinal administration of monteplase (recombinant)?

|                                    |                                                                                                                                                                                                                 |
|------------------------------------|-----------------------------------------------------------------------------------------------------------------------------------------------------------------------------------------------------------------|
| i. Treatment condition of interest | Subretinal administration of monteplase (recombinant)                                                                                                                                                           |
| ii. Population                     | Patients with SMH defined by the inclusion criteria (severe sub-macular hemorrhage in which spontaneous resolution is not expected, the bleed involves the fovea, and marked visual-acuity loss is anticipated) |
| iii. Endpoint                      | 1) Change in CFT from baseline at Week 12.
2) BCVA (logMAR equivalent) at Week 12.
3) Change in BCVA (logMAR equivalent) from baseline at Week 12.                                                        |
| iv. Other intercurrent events      | See Table 3-1                                                                                                                                                                                                   |
| v. Population-level summary        | 1) Mean change from baseline to Week 12 in CFT measured by OCT.
2) Mean BCVA (logMAR equivalent) at Week 12.
3) Mean change from baseline to Week 12 in BCVA (logMAR equivalent).                         |

Rationale for the estimand: SMH causes an acute and severe visual impairment, and when it becomes chronic it induces irreversible neuro-retinal degeneration that affects visual prognosis. Even when the impact of VEGF-inhibitor uses after monteplase administration, or the use of tPA formulations for other diseases, is taken into account, the reduction of the hemorrhage, the presence or absence of hemorrhage displacement, and the degree of visual recovery are considered important to regulatory authorities and to those determining the therapeutic strategy for the target patient population. Although observation of visual recovery requires a long period,

the hemorrhage is naturally reabsorbed over time and many patients experience re-bleeding; therefore, long-term changes in CFT may be increasingly influenced by factors other than sub-retinal tPA administration. Consequently, the 3-month time point was selected as one of the assessment points for a secondary estimand.

Table 3-1 Other Intercurrent Events

| Intermediate events                                                             |                                                                                                                 | Reasons for occurrence                                                                                            | Primary estimand               | Secondary estimand             |                                 |                                                  |                                |                    |                                 |                                                                           |
|---------------------------------------------------------------------------------|-----------------------------------------------------------------------------------------------------------------|-------------------------------------------------------------------------------------------------------------------|--------------------------------|--------------------------------|---------------------------------|--------------------------------------------------|--------------------------------|--------------------|---------------------------------|---------------------------------------------------------------------------|
|                                                                                 |                                                                                                                 |                                                                                                                   | Central foveal thickness       |                                |                                 | Best-corrected visual acuity (logMAR equivalent) |                                |                    |                                 | Presence of hemorrhage measuring at least 1 optic-disc diameter           |
|                                                                                 |                                                                                                                 |                                                                                                                   | Change from baseline to Week 1 | Change from baseline to Week 4 | Change from baseline to Week 12 | Value at Week 4                                  | Change from baseline to Week 4 | Value at Week 12   | Change from baseline to Week 12 | Presence of hemorrhage measuring at least 1 optic-disc diameter at Week 4 |
| Vitreous re-operation                                                           |                                                                                                                 | Re-bleeding                                                                                           | Composite variable             | Composite variable             | Composite variable              | Composite variable                               | Composite variable             | Composite variable | Composite variable              | Composite variable                                                        |
|                                                                                 |                                                                                                                 | Ocular complications (endophthalmitis, retinal detachment, vitreous hemorrhage)                                   | Treatment policy               | Treatment policy               | Treatment policy                | Treatment policy                                 | Treatment policy               | Treatment policy   | Treatment policy                | Treatment policy                                                          |
| Sub-Tenon administration of triamcinolone acetate                               |                                                                                                                 | Macular edema                                                                                                     | Treatment policy               | Treatment policy               | Treatment policy                | Treatment policy                                 | Treatment policy               | Treatment policy   | Treatment policy                | Treatment policy                                                          |
| Withdrawal of consent / loss to follow-up                                       |                                                                                                                 | Withdrawal of consent for reasons that have a major impact on the evaluation items (e.g., serious adverse events) | Composite variable             | Composite variable             | Composite variable              | Composite variable                               | Composite variable             | Composite variable | Composite variable              | Composite variable                                                        |
|                                                                                 |                                                                                                                 | Withdrawal of consent or loss to follow-up for reasons other than those described above                           | Virtual                        | Virtual                        | Virtual                         | Virtual                                          | Virtual                        | Virtual            | Virtual                         | Virtual                                                                   |
| Implementation of rescue therapy                                                | Photodynamic therapy                                                                                            | Treatment of underlying disease                                                                                   | Treatment policy               | Treatment policy               | Treatment policy                | Treatment policy                                 | Treatment policy               | Treatment policy   | Treatment policy                | Treatment policy                                                          |
|                                                                                 | VEGF inhibitor – Treatment                                                                                      | Treatment of underlying disease                                                                                   | Treatment policy               | Treatment policy               | Treatment policy                | Treatment policy                                 | Treatment policy               | Treatment policy   | Treatment policy                | Treatment policy                                                          |
|                                                                                 | Intravitreal gas injection                                                                                      | Re-bleeding                                                                                                       | Virtual                        | Virtual                        | Virtual                         | Virtual                                          | Virtual                        | Virtual            | Virtual                         | Virtual                                                                   |
| Implementation of prohibited concomitant drugs / prohibited concomitant therapy | Defibrimid sodium                                                                                               | Hepatic central-vein occlusion                                                                                    | Treatment policy               | Treatment policy               | Treatment policy                | Treatment policy                                 | Treatment policy               | Treatment policy   | Treatment policy                | Treatment policy                                                          |
|                                                                                 | Intravenous, sub-retinal, or intravitreal administration of tPA preparations other than alteplase (recombinant) | Additional treatment for SMH                                                                                      | Virtual                        | Virtual                        | Virtual                         | Virtual                                          | Virtual                        | Virtual            | Virtual                         | Virtual                                                                   |
|                                                                                 |                                                                                                                 | Treatment of other diseases (acute myocardial infarction, cerebral infarction)                                    | Treatment policy               | Treatment policy               | Treatment policy                | Treatment policy                                 | Treatment policy               | Treatment policy   | Treatment policy                | Treatment policy                                                          |
|                                                                                 | Intravenous or intravitreal administration of alteplase (recombinant)                                           | Additional treatment for SMH                                                                                      | Virtual                        | Virtual                        | Virtual                         | Virtual                                          | Virtual                        | Virtual            | Virtual                         | Virtual                                                                   |
|                                                                                 |                                                                                                                 | Treatment of other diseases (acute myocardial infarction, acute pulmonary embolism)                               | Treatment policy               | Treatment policy               | Treatment policy                | Treatment policy                                 | Treatment policy               | Treatment policy   | Treatment policy                | Treatment policy                                                          |
|                                                                                 | Hemorrhage removal surgery                                                                                      | Additional treatment for SMH                                                                                      | Composite variable             | Composite variable             | Composite variable              | Composite variable                               | Composite variable             | Composite variable | Composite variable              | Composite variable                                                        |

§Including cases in which a tPA formulation (including alteplase (recombinant)) is administered via subretinal injection.

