factor (VEGF) inhibitors, the annual incidence of SMH associated with visual loss was estimated at 0.46 %. AMD is a leading cause of blindness in developed countries, and in Japan, macular degeneration including AMD ranks fourth among causes of visual disability. The prevalence of AMD is estimated at 8.7 % of the world population; because aging is the primary risk factor, a substantial increase in patients is projected worldwide, especially in Asia, during the era of global aging. In a large cohort study in Japan covering the entire population aged  $\geq 40$  years (approximately 76 million), about 246 000 active exudative AMD patients were identified between 2011 and 2018, and prevalence has steadily increased across almost all age groups  $\geq 65$  years. In Japan, the proportion of exudative AMD patients is higher than in Europe and the United States; consequently, the number of SMH cases are expected to rise with the increasing patient population. RAM occurs in the elderly, is more common in women, and is strongly associated with hypertension and arteriosclerosis. The visual prognosis of RAM depends on macular pathology and may be complicated by intra-retinal hemorrhage or secondary macular holes; consequently, eyes with SMH in Japan are generally reported to have poor visual outcomes.

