#### 2.3.1. Risk Assessment

Adverse events that may occur with administration of monteplase (genetically engineered) include retinal toxicity (retinal morphological changes, etc.), increased sub-macular

hemorrhage, macular hole, vitreous hemorrhage, anterior chamber hemorrhage, endophthalmitis, elevated intra-ocular pressure, retinal detachment, corneal opacity, progression of cataract, etc. In addition to pharmacologic effects of the drug itself, events associated with vitreous surgery or intra-ocular tamponade are also encompassed.

To minimize these risks, the trial sites for this study shall be facilities that have prior experience with sub-retinal administration of tPA preparations, and patients at high risk will be excluded by the exclusion criteria.

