##### 9.3.1.1. Definition of the Endpoint

- Change: The change from baseline shall be calculated using the following formula.  
Change = measurement at week 1 – baseline value

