#### 9.3.2. Primary Analysis Method

For CFT, the 95 % confidence interval of the mean change from baseline at week 1 will be calculated, and a significance test will be performed using a t-test.

Intercurrent events shall be handled as follows.

For vitreous re-surgery for ocular-complication treatment, sub-Tenon injection of triamcinolone acetonide, rescue therapy with photodynamic therapy or VEGF inhibitors, and the administration of prohibited concomitant therapy for other diseases such as defibrotide sodium or tPA preparations (including monteplase) (adopting a treatment policy strategy approach), all observed values of the primary endpoint shall be used in the analysis. For withdrawal of consent or loss to follow-up not due to serious adverse events, intravitreal gas injection as rescue therapy, and the administration of prohibited tPA preparations (including monteplase) as additional treatment for sub-macular hemorrhage (adopting a hypothetical strategy approach), data collected after the occurrence of the intercurrent event shall be excluded from the analysis in order to evaluate the treatment effect without these influences. For vitreous re-surgery due to re-bleeding, withdrawal of consent due to serious adverse events, and hematoma-removal surgery using prohibited concomitant therapy (adopting a composite strategy), the change value of 0 shall be imputed as the worst value for the primary endpoint in cases where the intercurrent event occurred, and these cases shall be analyzed accordingly.

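### Retinal tissue lost at a macular hole counts as improvement in the primary endpoint, and no rule or sensitivity analysis deals with it

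*Protocol*

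**What the plan says.** Section 3 asks, for the primary objective, "what is the change in central foveal hemorrhage volume at the 1-week time point". The rationale for that estimand then describes the chosen variable: "CFT measured by OCT represents the combined thickness of the retina and the hemorrhage at the fovea". Section 9.3.1.1 defines the endpoint as "Change = measurement at week 1 – baseline value", so any fall in thickness is negative and therefore favourable.

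The protocol recognises macular hole in two places. The risk assessment (2.3.1) names it among the possible adverse events: "hemorrhage, macular hole, vitreous hemorrhage, anterior chamber hemorrhage". The background (2.2) says that RAM "may be complicated by intra-retinal hemorrhage or secondary macular holes". Section 9.9 requires at least three subjects with RAM.

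Table 3-1 has no row for macular hole. The nearest is vitreous re-operation for "Ocular complications (endophthalmitis, retinal detachment, vitreous hemorrhage", which follows treatment policy. For treatment-policy events section 9.3.2 states that "all observed values of the primary endpoint shall be used in the analysis". The same section assigns a change of 0, as the worst value, only to re-operation for re-bleeding, consent withdrawal because of serious adverse events, and surgical removal of the hemorrhage. Section 8.2.1 says to measure CFT by OCT but gives no rule for a fovea with a tissue defect.

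**The concern.** CFT is a sum of two parts, and the question concerns only one of them. When the retinal part falls because tissue is lost or displaced at a hole, the endpoint records it exactly as it records cleared blood. A complication that the protocol itself anticipates therefore moves the primary result towards success.

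The plan also becomes uneven in how it ranks outcomes. An eye classed as a treatment failure gets 0, while an eye with a new hole and unchanged blood gets a negative, favourable value. The Wilcoxon test in 9.3.2.1 uses the same changes, so it does not help. The supplemental analyses in 9.3.2.2 address repeated events, VEGF inhibitors and tPA given for other diseases, not holes. With one arm tested against 0, no control group carries the same artefact and could cancel it.

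At stake is the interpretation of the mean CFT change, which section 10.1.14 says may be provided for a marketing-authorization application.

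**Working it through.** **The plan's own figure.** Section 9.9 assumes an effect size of 0.7 (mean −120 µm, SD 170 µm), two-sided 5% and 80% power. For a one-sample t-test, the noncentral t distribution gives power 0.799 at n = 18 and 0.823 at n = 19, so 19 is reproduced. Dropout: 19 / 0.95 = 20. The point below does not affect the sample size.

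**Inputs**
- From the protocol: n = 20, SD 170 µm, planned mean −120 µm (9.9); minimum baseline CFT 300 µm (5.1).
- Assumed, because the protocol gives no figure: one or two holes among 20 eyes; retinal share lost at a hole R = 100 to 200 µm; baseline B up to 700 µm.

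**Split of the change in one eye.** CFT change = change in hemorrhage + change in retina. At a hole the second term is −R. If the blood has not moved, the eye scores −R, here −100 to −200 µm, which is better than the failure value of 0.

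**Shift of the mean per hole**
- Only the retinal share is spurious: R / 20 = 100/20 to 200/20 = 5 to 10 µm.
- CFT is recorded as 0 and the whole fall is counted, compared with scoring the eye 0: B / 20 = 300/20 = 15 µm at the protocol minimum, and 700/20 = 35 µm at the assumed upper baseline.

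Example for the second case, with the other 19 eyes at the planned mean: (19 × −120 − 300) / 20 = −129 µm and (19 × −120 − 700) / 20 = −149 µm, against (19 × −120 + 0) / 20 = −114 µm if the hole is scored 0.

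**Chance of a significant reduction when there is no true change otherwise.** Simulated one-sample t-test, n = 20, SD 170 µm, 400,000 runs, counting significant negative results. In the first row R is subtracted from the hole eye's random change; in the second row the change in the hole eye is fixed at −B.

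| What is counted at a hole | No hole | One hole | Two holes |
|---|---|---|---|
| Retinal share only, R = 100 to 200 µm | 2.5% | 3.2–3.9% | 4.1–5.8% |
| Whole baseline, B = 300 to 700 µm | 2.5% | 4.1–4.8% | 8.3–9.5% |

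The first row isolates the artefact. The second is an upper bound, because a fall to 0 also contains blood that really left the fovea.

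**The case against.** The strongest reply is that CFT is a disclosed and reasoned choice. Sections 3 and 4.2 say openly that it includes the retina, and justify it by objectivity, by its ability to capture flattening of pigment epithelial detachment, and by the exploratory Phase II purpose. This stands, and it is why the fix keeps CFT as the primary variable.

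A second reply is that holes would not be hidden. Fundus examination is scheduled at Week 1, adverse events are tabulated, and BCVA at Weeks 4 and 12 is a secondary endpoint. This also stands, but none of it changes the primary estimate or tests how far that estimate depends on such eyes.

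A third reply is that an eye whose CFT falls to 0 has lost its foveal blood as well, which is a real response to the stated question. That is correct. It means that only the retinal share is artefact, and that calling every such eye a failure in the primary analysis would be debatable. The plan also keeps re-operation for other ocular complications under treatment policy.

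A reader might infer more than the documents support:
- That retinal thinning is a listed harm. Section 2.3.1 says only "retinal toxicity (retinal morphological changes, etc"; thinning is not named. Tissue loss of any kind would act in the same direction, but no more can be said.
- That every hole produces a fall of at least 300 µm. This needs CFT to be recorded as about 0. If blood or a pigment epithelial detachment remains under the defect, or if the hole was already present at baseline, the fall is smaller.
- That efficacy would be largely produced by harm. The protocol gives no hole rate, and requiring three RAM subjects does not supply one.

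**Conclusion.** The gap is real and its direction is certain: retinal tissue lost at a macular hole counts as improvement in the primary analysis and in its only sensitivity test, and can outscore the plan's own failure value. Its size cannot be fixed from the protocol. Under the assumptions shown, one hole among 20 moves the mean by about 5 to 10 µm when only the retinal share is spurious, and by 15 µm or more when the whole baseline is counted. With no true change otherwise, the chance of a significant reduction rises from 2.5% to about 3–5% with one hole and about 4–9.5% with two. This is modest beside the planned 120 µm. It is a should-fix matter, not a must-fix one, and it leaves the choice of CFT and the sample size intact.

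**What to change.** 1. **Section 8.2.1.** State how CFT is recorded when the fovea has a tissue defect. From the same OCT image, record whether a full-thickness macular hole is present and, where readable, the height of the sub-foveal hemorrhage, at baseline and at each visit with a CFT endpoint (Weeks 1, 4 and 12). Say how a hole is classified when blood hid the fovea at baseline.
2. **Section 9.3.2.1.** Add a prespecified sensitivity analysis that repeats the primary analysis with a change of 0 for eyes with a new full-thickness hole. This is the worst value that section 9.3.2 already uses.
3. **Section 9.3.2.2.** Add a supportive analysis of the change in hemorrhage height, which addresses the primary clinical question directly.

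Moving macular hole into the composite strategy of the primary estimand is an option for the sponsor, not a required correction.

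The cost is two case report form fields read from images that the CFT endpoints need anyway, and a few sentences of text. The sensitivity result will be slightly less favourable if holes occur, and hemorrhage height may be unreadable in dense bleeds. The change should be made before outcome data are seen, so that it cannot appear driven by the results.
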